**Secondary outcomes**		
SIS 3.0	- Total score (0––100)	= Sum of domain scores
	- Perceived recovery (0–100%)	Collected by visual analogue scale
	- Domain scores (0–100%): strength, memory/thinking, emotion, communication, ADL/IADL, mobility, hand function, participation	$$=\frac{\text{Sum of Likert ratings}}{\textrm{Number of items}}\times 100$$
SRT	Of all six conditions:	
	- Reaction time	= Logarithmic mean of trial reaction times
	- Missed	Number of non-answered stimuli within 1500 ms
	- Mistakes	Number of reactions upon no stimulus
TMT A&B	- Time A, time B	Processing time of each sub-test
	- Mistakes A, mistakes B	Number of incorrect touches in each sub-test
	- B to A ratio	$$=\frac{\text{Time B}}{\textrm{ Time A}}$$
Stroop	For reading and naming:	
	- Interference tendency	= Median RT interference – median RT baseline
	Of all four conditions:	
	- Reaction time	= Median reaction time of all trials
	- Mistakes	Number of false reactions
NBT	- Correct	Number of correct responses (stimulus inquired a reaction and participant responded)
	- Omissions	Number of missed responses (stimulus inquired a reaction but participant did not respond)
	- Mistakes	Number of incorrect responses (stimulus inquired no reaction but participant responded)
	- Reaction time (correct)	= Mean reaction time of correct responses
	- Reaction time (mistakes)	= Mean reaction time of incorrect responses
MRT	- Accuracy	$$=\frac{\text{Number of correct responses}}{\textrm{ Total number of tasks}}$$
	- Reaction time	= Mean reaction time of correct responses
TUG	- Time TUG	= Mean time of the 3 motor single-task trials
	- Type of cognitive task	Serial subtraction or verbal fluency
	- Correct response rate single-task (CRR_single_)	= Mean CRR of the 3 cognitive single-task trials
		CRR $$=\frac{\text{Number of correct responses}}{\text{ Time}}$$
	- Time TUG-Cogn	= Mean time of the 3 dual-task trials
	- Correct response rate TUG-Cogn (CRR_dual_)	= Mean CRR of the 3 dual-task trials
	- Motor dual-task effect (DTE%_motor_)	$$=\frac{\text{Time TUG-Cogn - Time TUG}}{\textrm{Time TUG}}\times 100$$
	- Cognitive dual-task effect (DTE%_cognitive_)	$$=\frac{{\text{CRRdual-CRRsingle}}}{{\textrm{CRRsingle}}}\times 100$$
10MWT,	- Time	= Mean time for 10m of the three trials
preferred	- Gait speed (preferred)	= Mean gait speed
		Instruction: ‘Walk at a comfortable speed’
	- Cadence	= Mean steps/min
	- Stride length	= Mean stride length
	- Stride length variability	= Mean stride length variability

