Secondary cognitive outcomes include the following computer-based cognitive assessments:To assess alertness, a simple reaction test (SRT) (‘WAFA’ within the Vienna Test System, VTS, see the ‘Plans for assessment and collection of outcomes’) is applied. The SRT is a reliable and valid neuropsychological assessment for alertness [105–107]. It composes of six tests with visual and auditory stimuli, of which two evaluate intrinsic alertness (participant has to react to an appearing stimulus as fast as possible), two evaluate crossmodal-phasic alertness (a crossmodal warning stimulus precedes the actual stimulus and the participant has to only react to the actual and not the warning stimulus), and two evaluate unimodal-phasic alertness (a unimodal warning stimulus precedes the actual stimulus and the participant has to only react to the actual and not the warning stimulus) [107].Processing speed and cognitive flexibility, a sub-domain of executive functions, are assessed using the Trail Making test (TMT) (‘TMT—Langensteinbacher Version’ within the VTS), which is a widely used, reliable, and valid neuropsychological assessment [108–110]. The TMT consists of two parts: TMT-A assesses general information-processing speed; it asks to connect rising numbers (1–25) as fast as possible. TMT-B is used to test cognitive flexibility; the task is to connect rising numbers and letters alternatingly [111].To assess interference inhibition, another sub-domain of executive functions, the Stroop Interference test (‘STROOP’ within the VTS) is used [112]. The Stroop test is a widely used, reliable, and valid neuropsychological assessment testing the ability to inhibit the reaction to a more dominant stimulus in favour of the inquired reaction to a less dominant stimulus [113]. This assessment contains four sub-tests: two baseline and two interference conditions. In the first baseline condition, colour words are presented in grey font and the participant must select the correct colour (baseline reading). In the second baseline condition, coloured bars are presented, and the participant must select the correct colour (baseline naming). In the interference conditions, the colour words are shown in coloured fonts and the participant has to either select the correct colour of the word (interference reading) or of the font (interference naming) [114].To assess working memory and related cognitive functions, the N-back test (NBT) (‘NBV’ within the VTS) is used, which is a widely used, reliable, and valid neuropsychological test [115–117]. The participant is presented a row of letters and has to decide upon every letter whether it corresponds to the one shown N letters earlier [118]. In this study, the test condition *N* = 2 is used.Mental rotation ability, a sub-domain of visuospatial functions, is assessed using the mental rotation test (MRT) (‘3D’ within the VTS), which is based on the paradigm by Shepard and Metzler [119]. It determines the ability to mentally rotate abstract objects and has been used in stroke patients before [85, 120, 121]. Each item consists of a figure composed of a number of blocks. The participant has to imagine how the arrangement of the blocks looks when viewed from another perspective and choose the correct 2D-view from a selection of four possible solutions [122].

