Assumptions on the residuals of primary and secondary outcomes will be checked using the DHARMa package in R [147]. Appropriate actions will be taken if one or more assumptions are not met. All primary and secondary outcomes will be analysed following the standard intention-to-treat (ITT [148, 149]) principle using linear mixed-effects models (LMEM, lme4 package in R). Subject-specific random intercepts will account for within-subject correlations between time points. Follow-up scores (T2) of the outcomes will be the dependent variables of the models, while group (intervention vs. control, control being the reference), time (T0, T1, T2), and group x time interactions at T1 and at T2, respectively, will be included as independent variables (fixed effects). Baseline factors such as age, sex, and time since stroke will be considered as covariates. Missing data of whole measurement time points (i.e. of dropouts) will be accounted for with the ‘last observation carried forward’ method. For single missing data points (e.g. if a participant did not perform an assessment at one time point or a technical issue produced missing data at one time point), however, no data imputation will be performed as LMEMs can be fitted even if some outcome data are missing [145, 150]. For the outdoor walking assessment (OWA), high occurrence of missing data is expected, as ability to walk 400 m is not covered by the eligibility criteria and varying weather conditions on the measurement days may interfere with the assessment. Therefore, for the OWA outcome parameters, datasets of participants who did not perform the OWA at one or several time points will be excluded from the analysis. Significance will be set to *p* < 0.05. Effect sizes will be calculated as *r* (Bravais-Person correlation coefficient) and interpreted as small (*r* < 0.3), medium (*r* < 0.5), and large (*r* ≥ 0.5) [145].

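### N-back outcomes in Table 3: Omissions repeats Correct, no listed outcome combines hits with false alarms, and Reaction time (mistakes) is undefined at an error-free visit (minor)

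*Protocol article*

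**What the plan says.** The Secondary outcomes section gives the purpose of the test: "To assess working memory and related cognitive functions, the N-back test (NBT"). The task at N = 2 is a discrimination task: "The participant is presented a row of letters and has to decide upon every letter whether it corresponds to the one shown N letters earlier".

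Table 3 fixes five outcome variables for it:

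- Correct: the count of targets that the participant answered (hits).
- Omissions: the count of targets left unanswered (misses), which the table words as "Number of missed responses (stimulus inquired a reaction but participant did not respond").
- Mistakes: the count of non-targets that the participant answered (false alarms).
- Reaction time (correct): the average over the hits.
- Reaction time (mistakes): the average over the false alarms, which the table words as "Mean reaction time of incorrect responses".

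Under Statistical methods for primary and secondary outcomes {20a}, "All primary and secondary outcomes will be analysed following the standard intention-to-treat" principle with linear mixed-effects models, at p < 0.05. For single missing values, "no data imputation will be performed as LMEMs can be fitted even if some outcome data are missing". The examples given for that rule are an assessment not performed and a technical fault. A value that cannot exist because the participant made no errors is not mentioned.

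**The concern.** There are three separate issues.

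1. Every target is either a Correct or an Omission, so the two rows carry the same information.
2. The test is meant to show how well a participant tells targets from non-targets. Correct and Omissions depend on that ability, but also on how readily the participant presses. Mistakes depends on the same two things, with readiness acting the other way. If the arms differ in readiness, the three counts point in different directions, and the plan does not say which result speaks for working memory.
3. A mean over mistakes needs at least one mistake. At T1 and T2, who has a value depends on performance after randomisation, so the comparison is no longer between the randomised groups.

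At stake is how one secondary cognitive test is interpreted.

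**Working it through.** **Figures in the plan.** The article gives no figure for the N-back test: no target count, no non-target count and no expected error rate. The only stated number used below is the sample size of 38 (about 19 per group). It reproduces: the within-between interaction of a two-group, three-measurement ANOVA with f = 0.21, correlation 0.5 and α = 0.05 needs N = 38, with power 0.8003. Nothing below changes it.

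**Step 1: duplication.** With T targets for everyone (an assumption that the article neither states nor contradicts), Omissions = T − Correct. The correlation is −1. In a linear mixed model the coefficients change sign and the p-values are identical.

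**Step 2: a shift in response criterion only.** Assumed model: equal-variance signal detection, with hit rate H = Φ(d′/2 − c) and false-alarm rate FA = Φ(−d′/2 − c). Sensitivity is held at d′ = 2.0 and the criterion c moves from 0.6 to 0.

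- H goes from Φ(0.4) = 0.655 to Φ(1.0) = 0.841.
- FA goes from Φ(−1.6) = 0.055 to Φ(−1.0) = 0.159.

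| Assumed targets / non-targets | Correct | Omissions | Mistakes |
|---|---|---|---|
| 15 / 85 | 9.8 → 12.6 | 5.2 → 2.4 | 4.7 → 13.5 |
| 30 / 70 | 19.7 → 25.2 | 10.3 → 4.8 | 3.8 → 11.1 |

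Discrimination is unchanged by construction, yet two rows improve and one worsens.

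**Step 3: how often this would reach significance.** Simulation with 19 per arm, individual d′ with mean 2 and SD 0.6, individual c with mean 0.5 and SD 0.4, one arm shifted in c only, a two-sided t-test at a single visit, and 1,500 runs per setting. The d′ estimates used a correction for rates of 0 or 1.

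| Targets / non-targets | Shift in c | Correct | Omissions | Mistakes | d′ |
|---|---|---|---|---|---|
| 15 / 85 | 0.3 | 0.32 | 0.32 | 0.37 | 0.05 |
| 15 / 85 | 0.5 | 0.66 | 0.66 | 0.77 | 0.06 |
| 30 / 70 | 0.3 | 0.35 | 0.35 | 0.35 | 0.05 |
| 30 / 70 | 0.5 | 0.75 | 0.75 | 0.77 | 0.06 |

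With no shift, all four rates lie between 0.04 and 0.06. The t-test stands in for the planned mixed model, so these rates are indicative only.

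**Step 4: Reaction time (mistakes).** With NT non-targets and one common false-alarm rate, P(no mistakes at a visit) = (1 − FA)^NT. The expected number without a value is 38 times that.

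| FA | P(no mistakes), NT = 85 to 70 | Of 38 per visit |
|---|---|---|
| 0.5% | 0.65 to 0.70 | 25 to 27 |
| 1% | 0.43 to 0.50 | 16 to 19 |
| 2% | 0.18 to 0.24 | 7 to 9 |
| 5% | 0.01 to 0.03 | 0.5 to 1 |

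At FA = 10% and NT = 85 the probability is 0.9^85, about 0.0001, and the problem disappears.

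**The case against.** The strongest reply is that Mistakes is a listed outcome, analysed with the same model. In the simulation it picks up a pure criterion shift about as often as Correct does (0.35 to 0.77 against 0.32 to 0.75), and someone who pressed at every letter would record every non-target as a mistake. This stands. A reader might infer that readier responding would pass as improvement on the N-back as a whole. The documents do not support that, because the plan would show the cost in a third row. What it lacks is a rule or index for reading the three rows together.

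Other stronger readings also fail:

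- **That working-memory change could not be determined.** Hits, misses and false alarms are all recorded, so an index can be computed. It is just not named.
- **That the training makes participants respond more readily.** The article describes stepping movements that control games aimed at several cognitive functions. It says nothing of a shift in response readiness.
- **That error-free participants are dropped.** The mixed model keeps their other visits. Only someone without mistakes at every visit is lost, and only from this one outcome.
- **That the duplicate row adds a chance of a false positive.** Identical tests add none. The harm is one finding presented as two.

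It can also be said that derived scores belong in an analysis plan that is not shown. That has some force for a zero-mistakes rule. It has less for the outcome list, which Table 3 fixes variable by variable. The same table already defines derived contrasts for other tests (the Trail Making B to A ratio, Stroop interference tendency and dual-task effects), but none for the N-back.

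**Conclusion.** The point holds, as a minor one. Omissions duplicates Correct, given a common number of targets. No listed outcome measures discrimination, so a criterion shift alone would return two favourable results and one unfavourable result with nothing pre-specified to reconcile them. Reaction time (mistakes) compares subsets selected after randomisation. That the mixed model can be fitted to the available values does not remove the selection, because the mistake count is not in that outcome's model.

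The size rests on assumed target counts, sensitivity and false-alarm rates. The criterion argument and the undefined reaction time do not bite in the same range: the first was illustrated at false-alarm rates of about 5% to 16%, while the second matters at about 2% or lower. The Objectives section frames the secondary aims as exploratory, and neither the MoCA analysis nor the sample size is affected.

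**What to change.** - Name one accuracy outcome for the N-back that is tested and interpreted as working memory: hit rate minus false-alarm rate, or d′ with a stated correction for rates of 0 or 1. Under the model above only d′ is unaffected by the criterion. The simple difference is easier to read but still moves somewhat (0.655 − 0.055 = 0.600 to 0.841 − 0.159 = 0.682).
- Keep Correct and Mistakes as descriptive components.
- Drop Omissions as a separate test.
- Report Reaction time (mistakes) descriptively, by group and visit, with the number of participants contributing.

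The cost is one variable derived from counts already recorded and a few lines of text, with no new data. The downside is a small departure from the listed output variables. The trial was still running when the article was submitted. The change should be dated before the group comparison is run, or labelled post hoc if that has passed.

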**Intervention outcomes**	
Compliance rate (overall)	$$={\text{Mean}} \frac{\text{Number of attended training sessions}}{\textrm{ Number of offered training sessions}} \times 100$$
Compliance rates in each week (1–12)	
Adherence rate (overall)	$$={\text{Mean}} \frac{\text{Total attended training time}}{\textrm{ Total offered training time}} \times 100$$
Adherence rates in each week (1–12)	
Reasons for not attending or aborting a training session	
Perceived motor-cognitive task difficulty (overall)	Collected by visual analogue scale
Perceived m-c-task difficulty in each week (1–12)	
Perceived performance (overall)	Collected by visual analogue scale
Perceived performance in each week (1–12)	
**Further activities: usual care**	
- Frequency intense physical therapy (PT)	= Mean frequency per week of intense PT
- Volume/week intense PT	= Mean volume per week of intense PT
- Total volume intense PT	= Sum of the volume of all intense PT
- Frequency moderate PT	= Mean frequency per week of moderate PT
- Volume/week moderate PT	= Mean volume per week of moderate PT
- Total volume moderate PT	= Sum of the volume of all moderate PT
- Total volume PT	= Sum of the volume of all PT
- Types of PT	
- Frequency intense cognitive therapy (CT)	= Mean frequency per week of intense CT
- Volume/week intense CT	= Mean volume per week of intense CT
- Total volume intense CT	= Sum of the volume of all intense CT
- Frequency moderate CT	= Mean frequency per week of moderate CT
- Volume/week moderate CT	= Mean volume per week of moderate CT
- Total volume moderate CT	= Sum of the volume of all moderate CT
- Total volume CT	= Sum of the volume of all CT
- Types of CT	
- Total volume other therapies	= Sum of the volume of all other therapies
- Types of other therapies	e.g. massage
**Further activities: general**	
- Frequency intense physical activity (PA)	= Mean frequency per week of intense PA
- Volume/week intense PA	= Mean volume per week of intense PA
- Total volume intense PA	= Sum of the volume of all intense PA
- Frequency moderate PA	= Mean frequency per week of moderate PA
- Volume/week moderate PA	= Mean volume per week of moderate PA
- Total volume moderate PA	= Sum of the volume of all moderate PA
- Total volume PA	= Sum of the volume of all PA
- Frequency intense cognitive activity (CA)	= Mean frequency per week of intense CA
- Volume/week intense CA	= Mean volume per week of intense CA
- Total volume intense CA	= Sum of the volume of all intense CA
- Frequency moderate CA	= Mean frequency per week of moderate CA
- Volume/week moderate CA	= Mean volume per week of moderate CA
- Total volume moderate CA	= Sum of the volume of all moderate CA
- Total volume CA	= Sum of the volume of all CA
- Sedentary time per day	= Mean sedentary time per day

### Baseline factors

At baseline, the following information is recorded to describe the study population (see Table 2):Demographics (collected via baseline questionnaire): age, sex, years of education, marital statusOther characteristics (collected via baseline questionnaire): weight, height, handednessStroke diagnostic details (collected via baseline questionnaire): number of strokes, time point/type (ischemic, haemorrhagic)/lesion site/side and location of initial paresis of the (most recent) stroke, initial (if available), and current (at baseline) National Institutes of Health Stroke Scale (NIHSS [ 88])Clinical characteristics A (collected via baseline questionnaire): comorbidities (Charlson Comorbidity Index, CCI [ 89]), modified Rankin scale (mRS[ 90])Clinical characteristics B (collected by the assessor at the baseline measurement): Functional Ambulation Category (FAC [ 91]), Lower-Extremity component of the Fugl-Meyer assessment (FM-LE), Berg Balance Scale (BBS [ 92])

### Primary outcome

The primary outcome is global cognitive functioning measured by the total score of the Montreal Cognitive Assessment (MoCA) [93]. The MoCA is composed of several tests assessing different cognitive domains including attention, executive functions, working memory, short-term memory recall, visuospatial skills, and orientation [74]. The MoCA has been successful in detecting cognitive decline [94] and showed good reliability in stroke patients and healthy older adults [95–97] as well as fair to good responsiveness and validity [98] in chronic stroke patients [99]. The maximum achievable score is 30 points, where more points represent better cognitive functioning. For individuals with 12 or less years of education and a total score < 30, an additional point is added [93]. A MoCA score below 24 points indicates mild cognitive impairment in individuals after stroke [74, 100, 101], and an improvement of 1.22 points was found to be a clinically relevant change [99].

Global cognitive functioning, measured by the total score of the MoCA, covers the cognitive domains typically impaired after stroke. Further cognitive tests examining specific cognitive domains/functions will be implemented as secondary outcomes [102].

### Secondary outcomes

Health-related quality of life and perceived recovery are assessed using the total score and the single domain scores of the Stroke Impact Scale [SIS 3.0 [103]]. The SIS 3.0 is a stroke-specific questionnaire assessing the self-reported health status on 5-point Likert scales [98]. It encompasses eight domains (strength, memory/thinking, emotion, communication, ADL/IADL, mobility, hand function, and participation) and a visual analogue scale, where the perceived state of recovery is rated (0 to 100%) [98]. The final score lies between 0 and 100, where a higher score indicates better health-related quality of life. The German SIS (DE-SIS, translated and cross-culturally adapted) was found reliable and valid for the use in German-speaking stroke survivors [104].

Secondary cognitive outcomes include the following computer-based cognitive assessments:To assess alertness, a simple reaction test (SRT) (‘WAFA’ within the Vienna Test System, VTS, see the ‘Plans for assessment and collection of outcomes’) is applied. The SRT is a reliable and valid neuropsychological assessment for alertness [105–107]. It composes of six tests with visual and auditory stimuli, of which two evaluate intrinsic alertness (participant has to react to an appearing stimulus as fast as possible), two evaluate crossmodal-phasic alertness (a crossmodal warning stimulus precedes the actual stimulus and the participant has to only react to the actual and not the warning stimulus), and two evaluate unimodal-phasic alertness (a unimodal warning stimulus precedes the actual stimulus and the participant has to only react to the actual and not the warning stimulus) [107].Processing speed and cognitive flexibility, a sub-domain of executive functions, are assessed using the Trail Making test (TMT) (‘TMT—Langensteinbacher Version’ within the VTS), which is a widely used, reliable, and valid neuropsychological assessment [108–110]. The TMT consists of two parts: TMT-A assesses general information-processing speed; it asks to connect rising numbers (1–25) as fast as possible. TMT-B is used to test cognitive flexibility; the task is to connect rising numbers and letters alternatingly [111].To assess interference inhibition, another sub-domain of executive functions, the Stroop Interference test (‘STROOP’ within the VTS) is used [112]. The Stroop test is a widely used, reliable, and valid neuropsychological assessment testing the ability to inhibit the reaction to a more dominant stimulus in favour of the inquired reaction to a less dominant stimulus [113]. This assessment contains four sub-tests: two baseline and two interference conditions. In the first baseline condition, colour words are presented in grey font and the participant must select the correct colour (baseline reading). In the second baseline condition, coloured bars are presented, and the participant must select the correct colour (baseline naming). In the interference conditions, the colour words are shown in coloured fonts and the participant has to either select the correct colour of the word (interference reading) or of the font (interference naming) [114].To assess working memory and related cognitive functions, the N-back test (NBT) (‘NBV’ within the VTS) is used, which is a widely used, reliable, and valid neuropsychological test [115–117]. The participant is presented a row of letters and has to decide upon every letter whether it corresponds to the one shown N letters earlier [118]. In this study, the test condition *N* = 2 is used.Mental rotation ability, a sub-domain of visuospatial functions, is assessed using the mental rotation test (MRT) (‘3D’ within the VTS), which is based on the paradigm by Shepard and Metzler [119]. It determines the ability to mentally rotate abstract objects and has been used in stroke patients before [85, 120, 121]. Each item consists of a figure composed of a number of blocks. The participant has to imagine how the arrangement of the blocks looks when viewed from another perspective and choose the correct 2D-view from a selection of four possible solutions [122].

Secondary mobility and dual-task outcomes included the following assessments:The Timed Up and Go test (TUG), a reliable and valid assessment in stroke patients [123, 124], is conducted to analyse changes in mobility and dynamic balance. Participants are instructed to perform the TUG ‘as fast and safely as possible’. Time is measured from the moment the participant’s back leaves the backrest of the chair until it touches the backrest of the chair again [125].To assess mobility under dual-task conditions and dual-task effects, the TUG-Cognitive is also performed [126]. The TUG-Cognitive (TUG-Cog) is a reliable and valid assessment of dual-task mobility in stroke patients and healthy adults [125, 126]. A cognitive task is first executed in single-task mode during 60 s while being seated on a chair. After this, both tasks, the TUG and the cognitive task, are performed simultaneously, while participants are instructed to not prioritise one over the other. As cognitive task, serial subtraction of 3 from a random number between 50 and 100 (not in the row of three) will be used in participants who are able to complete this task [126, 127]. Participants, who are not able to accomplish serial subtraction, perform a verbal fluency task instead, naming nouns from categories (e.g. fruits, animals, cloths) starting with a specific letter [126, 127]. For all single- and dual-task trials, a familiarisation trial is performed before executing three test trials each. The TUG and TUG-Cog are conducted under laboratory conditions at the participating study centres.

Secondary gait outcomes included a 10-m walk test (10MWT) and an outdoor walking assessment (OWA) using inertial gait sensors to analyse temporal and spatial gait parameters.The 10MWT has been found reliable and valid in stroke patients [128]. The 10MWT is performed according to the protocol by Cheng et al. [128], where participants walk 14 m, where only the middle 10 m are timed. The participant starts walking at the 0-m mark, and the stopwatch is started as soon as the first foot crosses the 2-m mark and stopped again when the first foot crosses the 12-m mark, while the participant continues walking to the 14-m mark. At first, a familiarisation trial is performed followed by three trials at comfortable walking and three trials at fast walking speed. Participants are instructed to ‘walk at a comfortable speed’ and ‘walk as fast but safely as possible’, respectively. Participants use their usual walking aid if needed.The OWA is a 400-m walk following an outdoor route without stairs [129]. At each study centre, a suitable route nearby was pre-defined and all participants follow this same route. Participants use their usual walking aid if needed and wear proper footwear for an outdoor walk. They are instructed to ‘walk at a comfortable speed, as if they were on a stroll’. To ensure safety, participants are accompanied by two investigators.

